### 12.3. ANALYSIS POPULATIONS

Intent-to-Treat (ITT) Analysis Set: All randomized subjects. **This is the primary analysis set on which primary and secondary efficacy endpoints will be evaluated.** All subjects will be analyzed according to the treatment to which they were randomized.

Per-Protocol Analysis Set: The subset of subjects from the ITT analysis set in whom randomized treatment was initiated, who received the treatment to which they were randomized, who did not violate the inclusion/exclusion criteria, and who did not prematurely withdraw from the study (except due to death) by 60 days post-randomization.

Safety Analysis Set: The subset of ITT subjects in whom treatment was initiated.

This is the primary analysis set for the safety analysis. Subjects will be analyzed according to treatment received.

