#### **6.4. STUDY OBSERVATION PERIOD**

The Study Observation Period begins when the patient starts Control or Study Therapy and will continue up to a maximum of 168 hours from the time of Observation Start. It is expected that the patient will begin the Observation Period before the patient has reached 24 hours on CRRT.

This observation period has been broken into seven 24 hour time periods. It ends when the patient has reached 168 hours in the observation period or when the patient meets the termination criteria outlined in section 7.2 as determined by the Principal Investigator or Medical Team at the participating Clinical Site.

All tests are scheduled on a 24 hour cycle, or once a day, and can be scheduled to be drawn around each participating site's ICU blood drawing schedule, with the exception of any test that requires a specific draw frequency.

The following information will be obtained for patients enrolled in both study arms and recorded during the study observation period on a daily basis unless otherwise specified:

- **Vital Signs/Physical Assessment**
  - Temperature
  - Blood Pressure, heart rate – every 4 hours (+/- 1 hour)
  - Body weight
  - Sequential Organ Failure Assessment (SOFA Score)
  - Urine Output (previous 24 hours)
  - Net Fluid Balance (previous 24 hours)
- **Clinical Laboratory Tests**
  - CBC with differential – every 8 hours (+/- 2 hours)
  - BUN, Creatinine
  - Na, K, Cl, HCO3, Ca, Mg, Ionized Ca, PO4
  - ALT, AST, LDH, Bilirubin, ALP, Total Protein, Albumin, Glucose
  - Haptoglobin (on the last day of therapy only)
  - PT, PTT, INR
- **Respiratory**
  - Status – Ventilator support (yes/no; date of extubation)
  - If on Vent: Mode, FiO2, Settings- TV, PEEP, RR (q4h first 12 hrs (+/- 30 min) of observation period and then q12h (+/- 1 hour) thereafter)
  - If on Vent with an arterial line: Arterial Blood Gas (q4h first 12 hrs (+/- 30 min) and then q12h (+/- 1 hour) thereafter)
  - If on Vent without an arterial line: Arterial Blood Gas (once per 24 hours)
  - If not Vented: Supplemental oxygen requirements (q4h first 12 hrs (+/- 30 min) of observation period and then q12h (+/- 1 hour) thereafter)
- **Blood for Research**

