## **7. TREATMENT INTERRUPTIONS – DISCONTINUATION CRITERIA**

### **7.1. TREATMENT INTERRUPTION CRITERIA**

The SCD is to be used continuously along with CRRT and changed every 24 hours or at anytime the circuit exhibits significant clotting that impairs the functionality of the circuit. For patients randomized to either arm of the study, each participating site will follow their institution's protocol or standard of care in regard to replacement of the CRRT hemofilter and/or tubing.

In the event that a procedure is needed (e.g. CT-Scan, MRI), the CRRT or CRRT+SCD treatments may be interrupted for a maximum of 6 hours (cumulative) per 24 hour period. Cumulative interruption of greater than 6 hours in either the treatment or control arm will trigger the end of Observation Period and immediate initiation of the Follow-up period. These patients will not be removed from the study unless consent is withdrawn.

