### **7.2. TREATMENT DISCONTINUATION CRITERIA**

#### **7.2.1. CLINICAL CRITERIA**

Patients may be withdrawn from therapy (control or treatment) prior to hour 168 for a variety of reasons. When therapy is discontinued prior to hour 168, the follow-up period will immediately begin and data will continue to be collected per protocol.

The Principal Investigator will assign a primary reason for therapy termination utilizing the following categories, and if appropriate, one or more subcategories:

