#### 12.5. PRIMARY ENDPOINT

The primary endpoint in this trial is time to mortality through 60 days post-randomization. The Kaplan-Meier curve of time (days) to mortality through 60 days post-randomization will be presented, as will the Kaplan-Meier estimate of the 60 day mortality rate. In addition, the raw number and percentage of subjects who died by 60 days will be presented by treatment group. Treatment groups will be compared on time to mortality through 60 days using the log-rank test. The analysis will be carried out for the ITT (primary) and Per-Protocol (secondary) analysis set. It is anticipated there will be few randomized subjects who prematurely withdraw from the trial. Subjects who do not die will be censored at 60 days or at the last known time alive, whichever is earlier.

Due to one formal interim efficacy analysis following which the DSMB may recommend an increase in sample size (based on the observed treatment difference seen at the interim analysis) beyond the initially planned 172 randomized patients (see Section 12.8 for details), the final analysis comparing treatments on the primary endpoint does not use the conventional log-rank test p-value to determine if a statistically significant treatment difference exists. Instead it uses a weighted test statistic,  $T^*$ , proposed by Cui, Hung and Wang [33] in which the independent test statistics of the two stages (interim and final) are combined by pre-specified weights,  $w_1$  and  $w_2 = 1 - w_1$ , where  $w_1$  is the proportion of the total *initially* planned number of patients at which the interim analysis is performed. In the present case the trial is designed for 172 randomized subjects per group with an interim analysis after 50% of the patients achieve 60 day follow-up (or would have achieved 60 day follow-up had they not died or prematurely withdrawn). Thus, the planned information time proportions are  $w_1 = 50\%$  for first stage and  $w_2 = 1 - w_1 = 50\%$  for the second stage.

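### The Per-Protocol set drops patients who leave the study alive but keeps those who die, so membership depends on the primary endpoint and estimated mortality rises in any arm with withdrawals

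*Protocol*

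**What the plan says.** Section 12.3 makes ITT the primary set for efficacy. It defines the Per-Protocol set as the ITT patients "in whom randomized treatment was initiated, who received the treatment to which they were randomized, who did not violate the inclusion/exclusion criteria", and adds a last condition, "who did not prematurely withdraw from the study (except due to death) by 60 days post-randomization".

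Section 12.5 applies the log-rank comparison of time to death to both sets: "The analysis will be carried out for the ITT (primary) and Per-Protocol (secondary) analysis set". It also fixes the handling of incomplete follow-up: "Subjects who do not die will be censored at 60 days or at the last known time alive, whichever is earlier". It expects little of it: "It is anticipated there will be few randomized subjects who prematurely withdraw from the trial". For the ITT set it adds a multiple-imputation sensitivity analysis for patients who withdrew before day 60.

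Section 12.2 gives the planning hazards (0.01155 and 0.00718 per day) and the sample size (166 evaluable and 172 randomized per group).

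**The concern.** The withdrawal condition looks ahead to day 60 and exempts only death, which is the event being analysed. Take two patients who both complete their therapy. One withdraws consent alive on day 50 and is deleted with 50 event-free days. The other dies on day 50 and is kept as an event. Everyone whom the clause removes was alive when last seen, and it removes no observed death. The event count stays the same and the number at risk shrinks, so estimated mortality rises wherever there are withdrawals.

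The clause is also not needed. The analysis is time-to-event, and the censoring rule in section 12.5 already deals with a patient who leaves alive.

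What is at stake is how the Per-Protocol result is read. It is set beside the ITT result on the primary endpoint. The trial is open-label (section 4), so withdrawal could differ between arms, and a disagreement between the two analyses could then come from the exclusion rule and not from the treatment received.

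**Working it through.** **Inputs**
- Death hazards, section 12.2: λ = 0.01155/day (control) and 0.00718/day (SCD).
- Randomized and evaluable per group, section 12.2: 172 and 166. Implied attrition is (172 − 166)/172 = 6/172 = 3.5%.
- Assumptions, not in the protocol: withdrawal is independent of death risk and has a constant hazard η over 60 days; withdrawal rates other than 3.5%.

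**Step 1. Reproduce the planned mortality.** 1 − exp(−60 × 0.01155) = 0.500 and 1 − exp(−60 × 0.00718) = 0.350. Both match the protocol. The difference is 15.0 points.

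**Step 2. Formulas.** With competing death and withdrawal:
- W, the proportion withdrawn alive by day 60 = η/(λ+η) × [1 − exp(−60(λ+η))]
- D, the proportion seen to die by day 60 = λ/(λ+η) × [1 − exp(−60(λ+η))]
- Per-Protocol mortality = D/(1 − W), because the clause removes exactly the proportion W.

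**Step 3. Equal withdrawal.** Solve for the η that gives the stated W.

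| W per arm | Control: D/(1 − W) | SCD: D/(1 − W) | Difference |
|---|---|---|---|
| 3.5% | 0.4891/0.965 = 50.7% | 0.3430/0.965 = 35.5% | 15.1 points |
| 10% (assumed) | 0.4687/0.90 = 52.1% | 0.3296/0.90 = 36.6% | 15.4 points |

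Differences are taken before rounding. Both arms shift upward and the contrast barely moves.

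**Step 4. Late withdrawal.** If all withdrawals fall on day 50, the only deaths lost to observation are those due in the last 10 days. Per-Protocol mortality is then [m − W(1 − exp(−10λ))]/(1 − W), where m is the mortality from step 1. At 3.5%:
- control: (0.4999 − 0.035 × 0.1091)/0.965 = 51.4%
- SCD: (0.3500 − 0.035 × 0.0693)/0.965 = 36.0%

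Late withdrawal therefore roughly doubles the shift within each arm.

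**Step 5. Unequal withdrawal with no true effect.** Put λ = 0.01155 in both arms, with 10% withdrawn in one and 2% in the other (both assumed):
- 10% arm: 0.4687/0.90 = 52.1%
- 2% arm: 0.4938/0.98 = 50.4%

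The spurious difference is 1.7 points, against the arm with more withdrawal. With 5% against 2% it is 51.0% − 50.4% = 0.6 points.

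**Step 6. Check of the remedy.** In a simulation with 400,000 patients per arm under the same independence assumption, the Kaplan-Meier estimate with withdrawals censored returned the true mortality in every scenario, with equal and with unequal withdrawal. That simulation defined withdrawal as the rate before competing death, so its shifts from dropping withdrawals are slightly smaller: about 0.5 points per arm at 3.5%, and about 1.5 points of spurious difference for 10% against none.

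**The case against.** The strongest reply is that nothing decisive rests on this set. ITT is primary, the interim analysis uses ITT, and the Per-Protocol analysis carries no alpha and no stopping role. Two ITT analyses keep every withdrawal, one by censoring and one by imputation. At the protocol's own attrition the distortion is negligible: a simulated fixed-design log-rank test at 172 per arm with 3.5% withdrawal in each rejected under no effect in 4.5% of runs (ITT) and 4.6% (Per-Protocol), with power of 80.3% and 80.6%. All of this stands and limits the weight of the point. It does not justify the clause, which adds nothing that the censoring rule does not already do and which misleads if withdrawal is unequal. At 10% against 2% withdrawal, the false-positive rate in favour of the arm with less withdrawal rose from about 2% to about 5%.

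Three stronger readings are tempting, and the protocol does not support them.

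- *That the set ignores adherence because it keeps patients with very short exposure.* It does check initiation, arm received and eligibility. Therapy has a ceiling and no stated minimum (section 6.4: it "will continue up to a maximum of 168 hours from the time of Observation Start"). Early stopping is provided for in section 7.2.1: "When therapy is discontinued prior to hour 168, the follow-up period will immediately begin and data will continue to be collected per protocol". On interruptions beyond the limit, section 7.1 says: "These patients will not be removed from the study unless consent is withdrawn". Stopping early under these rules is not in itself a protocol violation, and an exposure condition could select on outcome too.
- *That the clause favours the device.* It does so only if withdrawal is higher in the control arm. With the excess in the SCD arm it shows false harm of the same size. The protocol does not indicate either imbalance.
- *That the trial's main conclusion is at risk.* The clause does not touch the ITT analysis.

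Independence of withdrawal and death risk is also an assumption. If patients who withdraw are sicker or healthier than those who stay, censoring is biased as well, and the shifts computed here would differ.

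**Conclusion.** The point holds within limits. The withdrawal clause makes Per-Protocol membership depend on the primary endpoint and raises estimated mortality in any arm with withdrawals. If withdrawal is independent of death risk and spread over 60 days, the rise is 0.7 points (control) and 0.5 points (SCD) at the implied 3.5%, and the contrast moves by about 0.1 point. A material bias in the contrast needs unequal withdrawal: about 1.7 points with no true effect at an assumed 10% against 2%, in either direction. The effect is confined to the secondary Per-Protocol analysis. The change is worth making because the clause serves no purpose in a time-to-event analysis, but it is not critical to the trial.

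**What to change.** In section 12.3, delete from the Per-Protocol definition the condition on withdrawal from the study by day 60, together with its exception for death. Leave the conditions on initiation, treatment received and eligibility as they are. Patients who withdraw alive then stay in the set and are censored at the last known time alive under the existing rule in section 12.5, as in the ITT analysis.

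The cost is the deletion of one clause. The Per-Protocol set becomes slightly larger, and the sample size, the alpha and the ITT analysis do not change.

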#### 12.4. DEMOGRAPHICS AND BASELINE CHARACTERISTICS

Baseline characteristics will be descriptively summarized for all subjects by treatment group for the ITT analysis set. Continuous measures will be summarized with sample size, mean, median, standard deviation, minimum and maximum; categorical measures will be presented with the counts and percents of subjects in each category. No statistical tests comparing treatments at baseline will be performed.

#### 12.5. PRIMARY ENDPOINT

The primary endpoint in this trial is time to mortality through 60 days post-randomization. The Kaplan-Meier curve of time (days) to mortality through 60 days post-randomization will be presented, as will the Kaplan-Meier estimate of the 60 day mortality rate. In addition, the raw number and percentage of subjects who died by 60 days will be presented by treatment group. Treatment groups will be compared on time to mortality through 60 days using the log-rank test. The analysis will be carried out for the ITT (primary) and Per-Protocol (secondary) analysis set. It is anticipated there will be few randomized subjects who prematurely withdraw from the trial. Subjects who do not die will be censored at 60 days or at the last known time alive, whichever is earlier.

Due to one formal interim efficacy analysis following which the DSMB may recommend an increase in sample size (based on the observed treatment difference seen at the interim analysis) beyond the initially planned 172 randomized patients (see Section 12.8 for details), the final analysis comparing treatments on the primary endpoint does not use the conventional log-rank test p-value to determine if a statistically significant treatment difference exists. Instead it uses a weighted test statistic,  $T^*$ , proposed by Cui, Hung and Wang [33] in which the independent test statistics of the two stages (interim and final) are combined by pre-specified weights,  $w_1$  and  $w_2 = 1 - w_1$ , where  $w_1$  is the proportion of the total *initially* planned number of patients at which the interim analysis is performed. In the present case the trial is designed for 172 randomized subjects per group with an interim analysis after 50% of the patients achieve 60 day follow-up (or would have achieved 60 day follow-up had they not died or prematurely withdrawn). Thus, the planned information time proportions are  $w_1 = 50\%$  for first stage and  $w_2 = 1 - w_1 = 50\%$  for the second stage.

Hence, two log-rank tests will be performed. The first (interim) log-rank test will be based on all patients who achieved 60-day follow-up (or would have achieved 60 day follow-up had they not died or prematurely withdrawn) at the time of the interim analysis. The log-rank test Z statistic for treatment effect from this model is denoted as  $Z^{(I)}$ . The second log-rank test will be based on all patients in the full analysis set at the end of the study. The log-rank Z statistic for treatment effect from this model is denoted as  $Z^*$ . Then define

$$Z^{(2)} = \frac{1}{\sqrt{1 - \frac{t_1}{t^*}}} Z^* - \frac{\sqrt{\frac{t_1}{t^*}}}{\sqrt{1 - \frac{t_1}{t^*}}} Z^{(1)}$$

where  $t_1$  = ratio of observed number of patients at the interim analysis to the *initially planned* total required number of randomized patients (172); and  $t^*$  = ratio of the number of randomized patients at the end of the trial to the initially planned total number of randomized patients (172).  $Z^{(2)}$  is independent of  $Z^{(1)}$  and captures the information about the treatment effect in  $Z^*$  that is not in  $Z^{(1)}$  [34].

At the final analysis, the test statistic used to compare treatments will be the weighted sum of  $Z^{(1)}$  and  $Z^{(2)}$  as defined above, using the square root of the planned proportions (square roots of  $w_1$  and  $w_2$  where  $w_1 = w_2 = 1 - w_1 = 0.5$ ) as the weights, respectively. Specifically, the weighted test statistic for the final analysis,  $T^*$ , is defined as:

$$T^* = \sqrt{w_1} Z^{(1)} + \sqrt{w_2} Z^{(2)}$$

This combined test statistic  $T^*$  will be used to test the treatment effect with respect to the primary outcome at the final analysis. This test statistic controls the overall type I error in the presence of a sample size increase. This has been confirmed by computer simulations.

The above is the primary analysis on the primary endpoint. Additional analysis on the primary endpoint will be as follows: to account for premature withdrawal from the study, the following analysis will also be performed on the ITT analysis set as a secondary sensitivity analysis: For patients who prematurely withdrew prior to 60 days post-randomization, missing mortality status will be imputed before carrying out the treatment comparisons. Imputation of missing mortality status will be carried out using the multiple-imputation logistic regression procedure using clinically relevant baseline characteristics as risk factors in the regression model (these characteristics will be fully specified in the study's statistical analysis plan). A total of 10 imputed data sets will be generated, and logistic regression comparing treatments on 60 day mortality status will be run on each data set. An assessment of overall treatment difference on 60 day mortality will then be generated from combining the logistic regression estimate of the treatment effect and the estimate of its standard error across the 10 data sets. This will not be done at the interim analysis, but only at the final analysis, at the same final significance level as will be used for the primary analysis.

For the primary (non-imputed) analysis on the ITT data set, the raw Kaplan-Meier estimates of mortality rate will be presented for each treatment group within each study center. An assessment of treatment-by-study center interaction effect will be carried out using Cox proportional hazards regression containing the main effects of treatment and center and the interaction effect of treatment-by-center. A treatment-by-center interaction effect that is not significant at the 0.15 level of

significance, or that is significant but only quantitative in nature, will not preclude pooling of patients across study centers for the primary endpoint analysis. Prior to breaking the randomization blind, study centers with less than 10 subjects will be pooled with other study centers located in similar geographic regions.

All enrolled patients will receive standard intensive care treatment for patients undergoing CRRT or CRRT+SCD. Any mode of CRRT will be allowed (CVVH, CVVHD, and CVVHDF) and the modality of CRRT is not expected to affect performance of the SCD. The modality-by-treatment interaction will be assessed. Specifically, for the primary (non-imputed) analysis on the ITT data set, the raw Kaplan-Meier estimates of mortality rate will be presented for each treatment group within each modality. An assessment of treatment-by-modality interaction effect will be carried out using Cox proportional hazards regression containing the main effects of treatment and modality and the interaction effect of treatment-by-modality. A treatment-by-modality interaction effect that is not significant at the 0.15 level of significance, or that is significant but only quantitative in nature, will not preclude pooling of patients across modalities for the primary endpoint analysis.

